# Efficacy of naloxone in reducing postictal central respiratory dysfunction in patients with epilepsy: study protocol for a double-blind, randomized, placebo-controlled trial

**DOI:** 10.1186/s13063-016-1653-1

**Published:** 2016-11-03

**Keywords:** Epilepsy, SUDEP, Opioids, Naloxone

## Abstract

**Background:**

Generalized tonic-clonic seizures (GTCSs) are the main risk factor for sudden unexpected death in epilepsy (SUDEP). Experimental and clinical data strongly suggest that the majority of SUDEP results from a postictal respiratory dysfunction progressing to terminal apnea. Postictal apnea could partly derive from a seizure-induced massive release of endogenous opioids. The main objective of this study is to evaluate the efficacy of an opioid antagonist, naloxone, administered in the immediate aftermath of a GTCS, in reducing the severity of the postictal central respiratory dysfunction.

**Methods/design:**

The Efficacy of Naloxone in Reducing Postictal Central Respiratory Dysfunction in Patients with Epilepsy (ENALEPSY) study is a multicenter, double-blind, randomized, placebo-controlled trial conducted in patients with drug-resistant focal epilepsy who are undergoing long-term video-electroencephalogram (EEG) monitoring (LTM) in an epilepsy monitoring unit (EMU). We plan to randomize 166 patients (1:1) to receive intravenous naloxone (0.4 mg) or placebo in the immediate aftermath of a GTCS. Because inclusion in the study needs to take place prior to the occurrence of the GTCS, and because such occurrence is observed in about one-fourth of patients undergoing LTM, we plan to include a maximum of 700 patients upon admission in the EMU. The primary endpoint will be the proportion of patients whose oxygen saturation is <90 % between 1 and 3 min after the end of a GTCS. Secondary outcomes will include the following: the proportion of patients who show postictal apnea, the occurrence and duration of postictal generalized EEG suppression, the total duration of the postictal coma, postictal pain, and the number of patients who have a second GTCS within 120 min after the intravenous injection.

**Discussion:**

The demonstration of naloxone’s efficacy on the severity of postictal hypoxemia will have two primary consequences. First, naloxone would be the first and only therapeutic approach that could be delivered immediately to reverse postictal apnea. Second, demonstration that an opioid antagonist can effectively reduce postictal apnea would pave the way for an assessment of a preventive therapy for SUDEP targeting the same pathophysiological pathway using oral administration of naltrexone.

**Trial registration:**

ClinicalTrials.gov identifier: NCT02332447. Registered on 5 January 2015.

**Electronic supplementary material:**

The online version of this article (doi:10.1186/s13063-016-1653-1) contains supplementary material, which is available to authorized users.

## Background

Sudden unexpected death in epilepsy (SUDEP) is defined as sudden, unexpected, witnessed or unwitnessed, nontraumatic, and nondrowning death in patients with epilepsy, with or without evidence of a seizure and excluding documented status epilepticus, in which postmortem examination does not reveal a toxicologic or anatomic cause of death [1]. SUDEP primarily affects young adults with drug-resistant epilepsy, with an incidence of about 0.4 %/year [2]. Among the SUDEP risk factors that have been individualized so far [2], the presence and frequency of generalized tonic-clonic seizures (GTCSs), either primary or secondary generalized), were found to represent the main ones, with an OR >15 for patients with three or more GTCSs per month [3].

There is currently no effective treatment to prevent SUDEP, apart from optimizing antiepileptic drugs (AEDs) [2, 4]. As underscored by the World Health Organization, there is an urgent need to develop specific therapeutic approaches to tackle this issue [5]. Considering that patients with the highest risk of SUDEP are young adults who have drug-resistant epilepsy with frequent GTCSs, it has been suggested that research on SUDEP prevention should be focused on this specific population [3, 6].

Although the exact pathophysiologic mechanisms that lead to SUDEP remain unknown [2, 7], most of the evidence lends support to the predominant role of central respiratory dysfunction [8]. Experimental and clinical data strongly suggest that most SUDEP results from a postictal respiratory dysfunction progressing to terminal apnea, followed by cardiac arrest [8, 9]. In addition, postictal generalized electroencephalogram (EEG) suppression (PGES), which is another factor associated with SUDEP [10], might primarily represent an ancillary marker of profound postictal hypoxemia [11]. Importantly, the central respiratory dysfunction that leads to SUDEP typically occurs between 1 and 3 min after the end of a GTCS [9], supporting the view that central respiratory dysfunction might be at least partly triggered by the release of neurotransmitter involved in seizure termination [8]. In this context, there might be a short time window during which this mechanism might be reversed by an appropriate treatment [8].

Animal studies suggest that seizure-related release of endogenous opioid peptides participate in termination of seizures [12]. In patients with epilepsy, functional imaging studies have confirmed that seizures induce release of endogenous opioids [13, 14]. The brainstem respiratory centers contain the highest density in opioid receptors [15], accounting for respiratory depression being one of the cardinal symptoms of opioid overdose [16, 17].

Our hypothesis is that SUDEP results partly from postictal apnea promoted by a GTCS-induced massive release of endogenous opioids, and that an opioid antagonist could represent an effective preventive treatment for SUDEP [8]. This could be achieved by chronic administration of naltrexone, an opioid antagonist that has been used in a large population of patients with chronic alcoholism at high risk of seizures, without showing any proconvulsive effect. This is a crucial feasibility issue because antagonizing a mechanism thought to participate in seizure termination could theoretically aggravate seizures.

Before evaluating the efficacy of chronic administration of naltrexone, it is legitimate to perform a proof-of-concept study by testing the acute effect of an equivalent injection treatment (naloxone) in the immediate aftermath of GTCS recorded in the hospital during video-EEG monitoring of patients with refractory epilepsy. One-third of these patients develop postictal respiratory dysfunction and hypoxemia [18], which should be reduced by our intervention if our hypothesis is correct.

## Methods/design

The Efficacy of Naloxone in Reducing Postictal Central Respiratory Dysfunction in Patients with Epilepsy (ENALEPSY) study is a multicenter, double-blind, randomized, placebo-controlled trial (Fig. 1 and Additional file 1: Standard Protocol Items: Recommendations for Interventional Trials [SPIRIT] checklist). The main objective of the study is to evaluate the efficacy of 0.4 mg intravenous naloxone versus placebo administered in the immediate aftermath of a GTCS in reducing the severity of the postictal central respiratory dysfunction occurring 1–3 min after the end of the seizure, as measured by peripheral oxygen saturation measured by pulse oximetry (SpO_2_).

**Fig. 1 Fig1:**
[figure not shown]
Flowchart of the trial. *EEG* Electroencephalogram, *EKG* Electrocardiogram, *GTCS* Generalized tonic-clonic seizure, *SEEG* Stereoelectroencephalography, *SpO*
_*2*_ Peripheral oxygen saturation measured by pulse oximetry

### Study setting

The study will be conducted with patients who have drug-resistant focal epilepsy investigated with long-term scalp video-EEG or video-stereoelectroencephalography (video-SEEG) in 1 of the 15 participating epilepsy monitoring units (EMUs) in France (see Additional file 2). The modalities of the video-EEG monitoring and patient management will be consistent with current practices and will be similar across all participating centers, including modalities of invasive recording using SEEG in the ten EMUs that perform both video-EEG and video-SEEG monitoring. Specifically, all of them undergo systematic recording of SpO_2_ coupled with video-EEG. The reliability of the measurement of SpO_2_ during seizures has been validated by two studies in which researchers carried out this type of monitoring [18, 19].

### Study duration

Recruitment into the trial commenced in July 2015 and is anticipated to be completed in July 2018. The duration of participation of each patient in the trial will be a maximum of 36 days. Long-term video-EEG/video-SEEG monitoring typically lasts between 7 and 15 days, and occasionally up to 21 days. However, the total duration of monitoring will be variable across patients, defined by clinical parameters, specifically the occurrence of a sufficient number of seizures to allow conclusions to be drawn about the localization of the seizure onset zone. For safety reasons, a phone visit will be held 15 days after the end of the monitoring.

### Participants

About 25 % of patients with drug-resistant partial epilepsy who are undergoing long-term video-EEG monitoring develop at least one focal secondary generalized tonic-clonic seizure (sGTCS) [18, 20, 21]. However, these patients cannot be individualized a priori. Therefore, all adult patients with drug-resistant epilepsy who will undergo long-term video-EEG monitoring in one of the participating centers will be included in the study according to the following inclusion criteria:Adult patients (≥18 years) with drug-resistant focal epilepsyPatients undergoing long-term video-EEG or video-SEEG monitoring in one of the participating centers to record and characterize their seizuresPatients who provide written informed consent to participate in the studyPatients affiliated with the French health care system

Patients fulfilling one or more of the following exclusion criteria will not be eligible for inclusion:Children (<18 years)Pregnant or breastfeeding womenHypersensitivity to naloxoneHistory of severe heart disease (i.e., myocardial infarction, heart failure disorder, arrhythmia severe hypertension)Ongoing opioid treatment, including both pure agonists and partial agonistsAddiction to opioids, heroin, or any similar substanceParticipation in another drug clinical trial within the last 2 months

Patients who have an sGTCS during the long-term video-EEG or video-SEEG monitoring while being supervised by a nurse or a physician will be randomized to receive intravenous naloxone (0.4 mg) or placebo.

As indicated in the exclusion criteria, naloxone will not be allowed for patients receiving ongoing opioid treatment, including both pure agonists and partial agonists. Therefore, patients receiving ongoing opioid treatment will be excluded. However, in the context of presurgical evaluation, especially for patients who undergo invasive recording with SEEG, the management of pain might require temporary administration of an opioid agonist. In such patients, short-lasting administration of opioid treatment following inclusion will be authorized, except for extended-release formulations of morphine. However, this will result in temporary ineligibility for randomization during the 12 h following the last opioid administration. If pain management requires administration of opioid treatment during 3 consecutive days, the patient will be excluded from the study.

### Interventions

Naloxone is a specific opioid antagonist without partial agonist activity. Intravenous administration has been approved in France since 1977 for the treatment of acute opioid overdose. In this indication, the recommended starting dose is 0.4 mg [16]. In acute opiate overdose, the delay between intravenous injection and awakening ranges from 30 s to 2 min, and its apparent duration of action is 20–90 min [16]. No epilepsy-related alert has been reported for this product. Naloxone administration will consist of naloxone hydrochloride dihydrate (0.4 mg/ml) packaged in 1-ml vials that can be intravenously administered to the patient without additional dilution. The placebo will be isotonic sodium chloride with preparation in 1-ml vials.

### Blinding and randomization

To avoid any follow-up or measurement bias, the patient, the supervising nurse, or the physician and the investigator will not be aware of the nature of the administered treatment. To respect the blinding and to ensure indistinguishability, preparations of both naloxone and placebo will be centralized by the pharmaceutical department of Hospices Civils de Lyon. The study drugs will then be distributed to the pharmacies of other investigator sites and stored at room temperature. Because of urgent need of treatment in case of occurrence of GTCS, one or more study treatments will be stored at room temperature in each EMU according to the expected number of randomizations at each center

Randomization will be centralized, stratified by center, and balanced by block of patients. For each study center, randomization lists will be prepared by the clinical research unit of Hospices Civils de Lyon. The pharmaceutical department of Hospices Civils de Lyon will prepare numbered batches according to the randomization lists.

In case of the occurrence of a GTCS, the affected patient will be randomized in a 1:1 ratio and assigned to the naloxone group or the placebo group. The batch number will be registered in the patient’s case report form. All digital data (video, EEG, respiration, SpO_2_) will be centralized and evaluated in blinded fashion with other data by the coordinator investigator of the study, who will not be involved in the video-EEG monitoring of the included patient.

If case of occurrence of a serious adverse event, the Antipoison and Toxicovigilance Center of Lyon will proceed to unblinding 24 h/24 h upon request by the study coordinator, the investigators, or the sponsor. A detailed written procedure for unblinding will be provided to all persons involved.

### Study conduct

All included patients will benefit from continuous monitoring of SpO_2_ and will be have a peripheral venous catheter inserted throughout the video-EEG/video-SEEG. During video-EEG/video-SEEG, patients are continuously supervised by one or two specialized nurses during the daytime at all participating centers. This continuous supervision allows immediate intervention in case of occurrence of a seizure. In six centers, patients are supervised by one specialized nurse during the night, whereas they are not supervised in the other centers. Given this organization of some EMUs, a GTCS might occur during a period without supervision. Unsupervised GTCS will not result in randomization, and the patient will remain eligible for randomization in case of occurrence of another GTCS during the monitoring. Inclusion in the study will not modify antiepileptic drug withdrawal, the management of which will remain at the discretion of each center.

In case of occurrence of a GTCS, patients will be randomized (1:1) into one of two groups: a single dose of 1 ml of either (1) naloxone or (2) placebo will be administered by the supervising nurse or physician, using direct intravenous injection. The evolution from a focal seizure to a GTCS being gradual, and the total duration of the seizure ranging from 2 to 3 min, the injection will be prepared during the course of the seizure. Given the assumptions about the role of endogenous opioid release in the spontaneous termination of seizures, naloxone will be administrated immediately after the end of the GTCS and not before. Specifically, treatment administration will be performed within the 2 min following the end of the GTCS.

Immediately after the administration of the treatment, the supervising nurse or physician will monitor respiratory movements to detect absence of chest expansion, SpO_2_, heartbeat and blood pressure, recovery of consciousness and pain, using a visual analogue scale. In patients with SpO_2_ < 85 % during >2 min after the injection of the study drug, O_2_ will be administered using a high-concentration breathing mask (15 L/min). Occurrence of one or more GTCSs during the 2 h following treatment administration will be monitored.

All digital data (video, EEG, respiration, SpO_2_) will be centralized and evaluated blind to other data. An automatic and objective analysis of SpO_2_ data will be performed using a specific detection algorithm that allows automatic detection and quantification of SpO_2_ and electrocardiogram variations.

### Outcome measures

#### Primary endpoint

The primary endpoint is the proportion of patients whose SpO_2_ is <90 % during at least 5 s between 30 s and 5 min after the onset of intravenous injection of the study drug in the immediate aftermath of a GTCS. The delay between the end of the seizure and administration of the treatment will be precisely determined by the video recording of the event, given that the nurse or physician who will administer the study drug will be required to both loudly order “injection” and raise an arm at the onset of injection. Previous studies have shown that the measurement of SpO_2_ is reliable in the vast majority of seizures, including GTCSs [18, 19]. To eliminate artefactual changes of SpO_2_, however, the criterion of hypoxemia duration of at least 5 s is required.

#### Secondary endpoints

##### Efficacy endpoints

Number of patients who show postictal apnea, defined as the absence of chest expansion during a period >10 s between 1 and 3 min after the end of the GTCSNumber of patients for whom O_2_ administration is required within the 10 min following the end of a GTCSNumber of patients for whom cardiorespiratory rescue procedure is required within the 10 min following the end of a GTCSTotal duration of the postictal generalized EEG suppression, defined as lack of detectable EEG activity >10 μV in amplitude on all leads [10]Total duration of the postictal coma, defined as the delay between the end of the seizure and the recovery of consciousness assessed by the ability to meet one single verbal command (handshake)

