### Statistical analyses

The primary analysis will be based on the intention-to-treat principle, including all randomized patients with usable records for SpO_2_. The proportion of patients whose SpO_2_ is <90 % during at least 5 s between 30 s and 5 min after the onset of intravenous injection of the study drug in the immediate aftermath of a GTCS will be presented in each group (naloxone and placebo) with the corresponding exact 95 % CI. These proportions will be compared between the two groups using Pearson’s chi-square test (or Fisher’s exact test if conditions for the chi-square test are not fulfilled).

A per-protocol analysis of the primary endpoint will also be performed in the population, which will comprise all randomized patients with usable records for SpO_2_ having no major protocol deviation such as patients in whom the onset of intravenous injection of the study drug was within the 2 min following the end of the seizure (whereas those in whom the study drug was administered >120 s after the end of the seizure will be excluded). Secondary endpoints will be compared between groups using Pearson’s chi-square test, Fisher’s exact test, Student’s *t* test, or the Wilcoxon-Mann–Whitney test, depending on the variable studied. The significance level will be set at 0.05.

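### The postictal apnea endpoint is timed from seizure end, so when the injection comes more than 60 s after the seizure, part of its window precedes dosing

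*Protocol article*

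**What the plan says.** Three timings in the Protocol article matter here.

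- **Apnea (Secondary endpoints, Efficacy endpoints).** A patient has postictal apnea if there is "the absence of chest expansion during a period >10 s between 1 and 3 min after the end of the" GTCS. The clock starts at seizure end.
- **Injection (Study conduct).** The intention is that "naloxone will be administrated immediately after the end of the GTCS and not before". The operational limit is that "treatment administration will be performed within the 2 min following the end of the GTCS".
- **Primary endpoint (Primary endpoint).** Hypoxemia is sought "between 30 s and 5 min after the onset of intravenous injection of the study drug". The clock starts at injection, and the first 30 s are left out. The Sample size and Statistical analyses sections repeat this window. The Abstract words the primary endpoint as 1–3 min after seizure end; I take the three body sections as governing.

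The article does not restrict the apnea count to time after injection. Under Statistical analyses, exclusion of injections later than 120 s is described only for the per-protocol analysis of the primary endpoint. The main analysis of that endpoint keeps late injections: "The primary analysis will be based on the intention-to-treat principle, including all randomized patients with usable records" for SpO2.

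**The concern.** Apnea is the mechanism that the trial hopes to show is reversed, so this secondary endpoint will be read closely beside the primary. It is a yes/no outcome for each patient. One absence of chest expansion longer than 10 s inside the window settles the patient's status. If that happens after the first minute but before a later injection, the patient counts as an event whichever vial was drawn.

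Such events enter both arms alike and pull the observed difference toward zero. The apnea result could then disagree with the hypoxemia result simply because the two are timed from different origins, and a reader could mistake this for evidence about mechanism.

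**Working it through.** The plan gives no figure on this point to reproduce. The check is window arithmetic.

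**Inputs**

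- Apnea window: 60 to 180 s after seizure end, length 120 s (Efficacy endpoints).
- Injection time *t*: 0 to 120 s after seizure end (Study conduct).
- Lag before an effect is looked for: 30 s after onset of injection, the protocol's own choice (Primary endpoint).

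**Formulas, for *t* from 0 to 120 s**

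- Share of the window before injection = max(0, *t* − 60) / 120.
- Share before the 30 s lag has passed = max(0, *t* + 30 − 60) / 120 = max(0, *t* − 30) / 120.

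| Injection, s after seizure end | Share before injection | Share before the 30 s lag has passed |
|---|---|---|
| 0 | 0 % | 0 % |
| 30 | 0 % | 0 % |
| 60 | 0 % | 30/120 = 25 % |
| 90 | 30/120 = 25 % | 60/120 = 50 % |
| 120 | 60/120 = 50 % | 90/120 = 75 % |

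**Average over injection times.** The article gives no distribution of the delay, so two assumptions show the range.

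- Uniform on 0–120 s. Before injection: (60² / 2) / (120 × 120) = 1,800 / 14,400 = 12.5 %. Before the lag has passed: (90² / 2) / (120 × 120) = 4,050 / 14,400 = 28 %.
- Uniform on 0–60 s. Before injection: 0 %. Before the lag has passed: (30² / 2) / (60 × 120) = 450 / 7,200 = 6 %.

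**From window time to treatment effect.** Let *f* be the share of control-arm apnea patients whose status is settled before the drug can act, and let *r* be the relative reduction among the rest. With control risk *p*, the naloxone risk is *p*[*f* + (1 − *f*)(1 − *r*)] = *p*[1 − (1 − *f*)*r*], so the observed relative reduction is (1 − *f*)*r* instead of *r*. The direction is clear. The size is not, because the article gives neither *f* nor *r* for apnea, and the share of window time is not the share of events.

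**With the primary endpoint's window.** It runs from *t* + 30 to *t* + 300 s after seizure end, that is 30–300 s for *t* = 0 and 150–420 s for *t* = 120. Neither time before injection nor time inside the 30 s lag is included, for any *t*. The window is 270 s long instead of 120 s, and its latest end is 420 s (7 min) after the seizure.

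**The case against.** The strongest defence is that the 1–3 min window is deliberate. The Background says that "the central respiratory dysfunction that leads to SUDEP typically occurs between 1 and 3 min after the end of a GTCS", and the main objective under Methods/design uses the same period. That stands as a reason to keep the count in view, but it describes when the dysfunction happens, not when the drug can alter it. The same reasoning did not stop the primary endpoint from being timed from injection.

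A second defence is that injection is meant to be immediate, with the syringe prepared during the seizure. This also stands in part: if nearly all injections fall within 30 s, the problem vanishes. But the plan allows 2 min and does not treat an injection at 60–120 s as a deviation.

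Several stronger readings are tempting, and the documents do not support them.

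- *Up to the whole window precedes drug action.* A reader might infer this from the statement under Interventions that "the delay between intravenous injection and awakening ranges from 30 s to 2 min". That interval is time to awakening in opiate overdose, not onset of a respiratory effect after a seizure. Only the 30 s lag has support in the plan.
- *Power for apnea falls by a stated amount.* The 33 % control rate under Sample size belongs to the SpO2 endpoint. No apnea rate is given, the trial is not powered on apnea, and such a calculation would have to equate window time with events.
- *Early apnea goes unobserved.* Study conduct says that after administration "the supervising nurse or physician will monitor respiratory movements to detect absence of chest expansion", but not that this bedside observation scores the endpoint. Video and respiration data are centralized and read blind.
- *Total duration of EEG suppression has the same flaw.* Total duration is a coherent randomized comparison. Scoring it as time remaining after injection would give zero in both arms to patients whose suppression had already ended, so it would not remove their dilution.

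**Conclusion.** The concern holds in a limited form. The apnea endpoint and the primary endpoint have different time origins, and the apnea window can include time before dosing. Under the plan's own rules the loss ranges from nothing (injection within 30 s) to 50 % of the window before dosing and 75 % before the 30 s lag has passed (injection at 120 s). The averages are 12.5 % and 28 %, or 0 % and 6 %, under the two assumed delay distributions. Injections later than 120 s would lose more.

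The 50 % figure needs no assumption about drug action. The 75 % figure rests on the protocol's 30 s lag. The averages rest on delay distributions that the article does not give.

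Because allocation is randomized and blinded, apnea before dosing is expected to be balanced between arms. A reader might infer a biased or invalid comparison; that does not follow. What follows is avoidable dilution of a mechanistic secondary endpoint. The conclusion on the primary endpoint is untouched. This is a cheap improvement, not a threat to the trial.

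**What to change.** Amend the definition of the apnea endpoint:

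1. Count apnea from 30 s to 5 min after the onset of injection, the window already used for the primary endpoint, keeping the existing duration criterion of more than 10 s.
2. Name the centralized video and respiration records, read blind, as the scoring source.
3. State how an apnea in progress when the window opens is handled, for example that it counts if more than 10 s of it fall inside the window.
4. Record apnea before injection as a separate descriptive variable.
5. Keep the 1–3 min count after seizure end as a supportive analysis.

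This changes measurement only. No treatment or timing of care is altered, and the signals and the injection time, marked on video, are already recorded. At publication 16 of the planned 166 patients had been randomized, so the change could be made blind and the stored records of those patients rescored.

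The costs are small but real. There are two apnea figures to report. The window is longer (270 s against 120 s), and for a late injection it extends well past the 1–3 min period named in the Background and the main objective, up to 7 min after the seizure. The supportive count preserves the link to that period.
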